### Prognostic variables of pain recurrences

#### Baseline laboratory assessment

All recruited participants with a history of recurrent NP episodes will attend an initial laboratory session (in Birmingham or Essex) during a period of symptom remission, and a battery of tests will be conducted to obtain a comprehensive evaluation (table 1). To minimise inter-site variability, all assessments will follow a standardised protocol, and both laboratories will use identical equipment from the same manufacturer. Participants will also be asked to complete a series of questionnaires to assess psychological features, including the Depression, Anxiety and Stress Scales (DASS-21),^43^ the short version of the Tampa Scale for Kinesiophobia (TSK-11),^44^ the EQ-5D-5L^45^ and pain processing characteristics, including the pain-self efficacy questionnaire,^46^ pain coping inventory^47^ and central sensitisation inventory.^48^ Overall, we will collect information on demographic characteristics, psychological and social factors, pain processing, neck kinematics, neck sensorimotor control and neck muscle function.

**Table 1 T1:** Collected data within physical, psychological and social domains

Domain	Feature extracted	Measurement tool
Demographics and Neck Pain characteristics	Age Sex BMI Ethnicity Number of other pain sites Number of previous pain episodes	Single question for each feature
Psychosocial factors	Stress (0–21) Anxiety (0–21) Depression (0–21) Kinesiophobia (11-44) Quality of life (0–100) Occupation Education level	DASS-21 DASS-21 DASS-21 TSK-11 EQ-5D-5L Single question Single question
Pain processing	Self-efficacy (0–60) Pain coping (12–48 active, 22–84 passive) Central sensitisation (0–100) Pressure pain threshold (kPa) Conditioned pain modulation	Pain Self-Efficacy Questionnaire Pain Coping Inventory Central sensitisation inventory Pressure algometry Cuff pressure algometry
Kinematic features and sensorimotor control	Average range of neck motion in flexion-extension, lateral flexion (R/L), rotation (R/L) Average speed of neck movement in flexion-extension, lateral flexion (R/L), rotation (R/L) Smoothness of neck movement (Jerk Index) in flexion-extension, lateral flexion (R/L), rotation (R/L) Neck proprioception (joint reposition error during right and left rotation)	All features obtained using wearable Inertial Measurement Unit (IMU, Sensamove 3D Cervical Trainer)
Neck muscle function and neuromuscular control	Craniocervical flexion performance Neck flexor strength and endurance Neck extensor strength and endurance Neck muscle co-contraction Neck muscle fatigue Upper trapezius strength	All features obtained using a hand-held dynamometer (NOD) and surface electromyography (Ultium EMG system)

BMI, body mass index; DASS-21, Depression, Anxiety, and Stress Scales; TSK-11, Tampa Scale for Kinesiophobia.

The same laboratory assessment will be conducted for the control group to identify potential candidate predictors (O.1), which have been selected for assessment based on findings from our previous work, current literature and PPIE input. The following physical tests will be performed in the same order as described below.

##### Pressure pain threshold

A pressure pain algometer (Somedic, Sweden) will be used to assess pressure pain threshold (PPT). PPT will be tested at the articular pillar of C2-C3 and C5-C6 facet joint, the upper trapezius muscle (midway between C7 and acromion), and over the tibialis anterior muscle (upper one-third of the muscle belly) over the dominant side.^49 50^ The measurement will be repeated three times, and the average will be taken for each site. This test has demonstrated high intrarater and interrater reliability in people with and without acute NP and can discriminate between those with and without NP.^50 51^

##### Conditioned pain modulation

Conditioned pain modulation (CPM) will be measured with cuff pressure algometry. An inflatable pressure cuff (NociTech, Denmark) will be mounted on the participant’s dominant arm. The pressure will be inflated, and the participant will indicate when they first detect pain (ie, pain detection threshold, PDT). The pressure will then continue to be increased until the subject’s tolerance limit, and this cuff pressure will be taken as the pressure tolerance threshold (PTT). Then the cuff will be immediately deflated. The same procedure will then be repeated on the non-dominant arm. To assess CPM, the cuff will be inflated to 70% of PTT on the non-dominant arm with PDT and PTT reassessed on the dominant arm. The CPM effect will be calculated as the conditioned PDT or PTT value minus the measures taken at baseline.^52^ User-independent cuff algometry has demonstrated high reliability for CPM assessment in people with chronic pain^53^ and has shown superior reliability compared with user-dependent assessments.^52^

##### Neck kinematics

A wearable Inertial Measurement Unit (IMU) system (myoMOTION Research Pro, Noraxon USA Inc.) with a sampling rate of 100 Hz will be used to analyse cervical kinematic outcomes while sitting. The IMU sensors will be placed via double-sided tape on the forehead and upper thoracic spine (T1). Participants will be asked to perform their active neck movements as far as they comfortably can go (flexion/extension, rotation, side flexion; randomised order using random number generator). Movements will be self-paced. They will be asked to do three repetitions for each plane of movement. One minute of rest will be provided between the different directions. The following features will be extracted: range of motion, speed of motion and smoothness of movement, measured by analysing the jerk index during active cervical movements.^54^ IMU sensors have high concurrent validity and reliability in the assessment of neck movements.^55^,^57^

##### Cervicocephalic relocation test

The same wearable IMU system (myoMOTION Research Pro, Noraxon USA Inc.) will also be used to test neck proprioception while sitting. Participants will be told to close their eyes and from a neutral starting position, subjects will perform active neck rotation and then they will return, as accurately as possible, to the initial position. The joint reposition error (absolute discrepancy between the initial and final position) will be analysed. Three repetitions will be performed for right and left rotation (random order). High reliability of IMU sensors and good-to-excellent agreement between IMU sensors and 3D motion capture have been demonstrated for the cervicocephalic relocation test.^58 59^

##### Craniocervical flexion test (CCFT)

Participants will perform the Craniocervical flexion test (CCFT) in a supine position. A handheld dynamometer will be used (NOD, OT Bioelectronica, Italy)^60^ to assess neck muscle strength, and surface electromyography (EMG) will be used to measure neck muscle activity. The handheld dynamometer, which will be used, is a device that has shown strong validity and high reliability for the assessment of neck muscle strength.^61 62^ Furthermore, the CCFT has high reliability, moderate convergent validity when compared with electromyography measures of neck muscles, and discriminative validity when testing people with and without NP.^63 64^ The NOD device will be placed behind the upper region of the neck. Two maximal isometric contractions (3–4 s) will be performed, and the force level will be recorded; 1 min rest will be provided between contractions. Next, participants will perform four contractions with different intensities: 20-40-60 and 80 per cent of the MVC of the CCFT. Each repetition will last 10 s, and 30 s of rest will be allowed between stages. During this test, visual feedback of the force output will be provided to participants. They will then perform a single sustained contraction at 40% MVC for 20 s. EMG signals will be recorded from the sternocleidomastoid muscle bilaterally using surface electrodes with a fixed 2 cm interelectrode distance.^65^ Surface electromyography will be measured with the Ultium EMG System (Noraxon, USA) using wireless sensors. The sampling frequency of EMG signals is 2000 Hz with the data converted to digital form by a 16-bit A/D converter, and a 10–500 Hz bandwidth filter is applied by the amplifier. Signals will be recorded and visually checked using the software myoRESEARCH 4 (Noraxon, USA).

##### Maximal and submaximal voluntary contractions

The same handheld dynamometer and surface electromyography system will be used to measure neck muscle activity during maximum and submaximal neck flexion and extension contractions. The activity of the sternocleidomastoid and splenius capitis muscles will be detected using surface electrodes with a fixed 2 cm interelectrode distance and placed bilaterally following guidelines for electrode placement.^65^,^67^ Flexion and extension isometric forces of the neck muscles will be assessed with the participants seated with their back supported and their torso firmly strapped to the seat back. Participants will be instructed to perform maximal neck flexion and extension against the dynamometer held by the assessor at the forehead and occiput respectively. Electromyographic measures of the superficial neck muscles have been shown to be reproducible and can discriminate between individuals with and without NP.^32 68 69^

Maximal isometric contraction while seated: following a period of familiarisation with the device, participants will be asked to perform two maximal contractions for both flexion and extension, which will be done in a random order. Each contraction will last 3–4 s, with 1 min rest between each repetition. The highest value for each direction will be considered as the reference maximum voluntary contraction (MVC) in order to calculate the submaximal force value. EMG signals will be recorded.

Submaximal contraction while seated: after 5 min of rest, participants will perform one submaximal isometric contraction in flexion and one in extension (order randomised for each participant) at 40% of MVC for 20 s. 5 minutes of rest will be provided between contractions. EMG signals will be recorded. Participants will be asked to rate their exertion using the Borg CR10 Scale (0–10) immediately following the completion of each sustained submaximal contraction.

Finally, participants will be asked to perform a shoulder shrug to measure the maximal voluntary contraction of the upper trapezius. The dynamometer will be placed over the participant’s acromion region by the investigator, who will resist the force exerted by the participant while they shrug their shoulder. Participants will be asked to perform two maximal contractions for each side, and the order will be randomised.

##### Neck flexor and extensor endurance

Neck flexion endurance will be measured with the patient in supine. The participant will slightly nod and then raise the head just above the examination table. For the test of neck extension endurance in prone, the head will be placed away from the examination table so that an inclinometer will be attached to the head to indicate 0 degrees when in neutral. Additionally, a 3-kg weighted strap will be secured around the head. The participant will hold the position until they have a change in head angle of five or more degrees for extension. Endurance time will be recorded for each test. A rest of 10 min will be given between the tests, and the tests will be conducted in a random order. A familiarisation of the movements will be given. Good to excellent reliability and validity, assessed by comparison with the Neck Disability Index, have been demonstrated for isometric muscle endurance tests in people with NP.^70 71^

### Second laboratory assessment during a NP episode

People in the recurrent NP cohort who develop a new painful NP episode after the baseline assessment and who agree to participate in a further laboratory session will return to the lab and the same tests and questionnaires performed during the baseline assessment will be conducted to evaluate changes in physical and psychological features during a painful episode (table 1). This will aid in identifying potential candidate predictors (O.1) that are influenced by pain and clinically relevant. Although such changes during a NP episode may represent a direct consequence of pain, this does not preclude their prognostic relevance. Features that are affected by pain and not fully restored during remission may persist or progressively worsen over time, potentially contributing to the development of future NP episodes.

### Outcomes of interest

The development of new NP episodes and their severity represent the main outcomes of interest in the recurrent NP cohort. To define the presence and severity of NP episodes, multiple questions will be collected through online questionnaires and by referring to the previous 2 weeks recall period (table 2). The collected information will be used to identify the number of days with NP during the 12-month follow-up. Furthermore, average and worst pain intensity (rated using a visual analogue scale 0–100) during new NP episodes over the 12 months will be aggregated to define the severity of NP. Based on established cut-points for grading chronic musculoskeletal pain,^72^ participants will then be classified into four severity groups: No pain (score of 0), mild pain (score of 1–34), moderate pain (score of 35–64) and severe pain (score >64). These two continuous and ordinal outcomes (ie, days with NP and severity of NP) will be the dependent variables used to develop the prediction models. Although we recognise that some participants might develop chronic pain during the follow-up, we decided to specifically focus on the frequency and severity of new NP episodes to better fit the fluctuating nature and symptom trajectory of people with recurrent NP.

**Table 2 T2:** Collected data on neck pain recurrences

Domain	Features extracted	Measurement tool
Recurrent episodes	Number of days with NP Average and worst NP intensity (VAS, 0–100) NP interference in daily activities (VAS, 0–100) NP interference in recreational, social and family activities (VAS, 0–100) NP interference with work (VAS, 0–100) Number of days using medication for NP relief Number and type of treatment received	Single questions

NP, neck pain; VAS, visual analog scale.

#### Follow-up assessment of new NP episodes and other factors

During the 12-month follow-up period, we will monitor the presence of new NP episodes. Specifically, people recruited in the recurrent NP cohort will receive an email with a link to an online questionnaire every 2 weeks throughout the entire 12-month follow-up period, commencing 2 weeks after the baseline assessment. This questionnaire seeks information on new NP episodes (table 2), and it will be sent automatically using the REDCap system, which is a secure, web-based application designed to support data capture for research studies. Reminders will be sent via email every 24 hours for a maximum of three consecutive days. A frequency of 2 weeks has been chosen to reduce the risk of recall bias and is informed by our PPIE group, which indicated that 2 weeks represents a tolerable amount of time for follow-up questionnaires over 12 months. In addition to information on new NP episodes, online follow-ups will also seek information on other environmental, behavioural and psychosocial factors including perceived stress, fatigue, quality of life, social support, level of physical activity, average sleep hours and quality and work-related factors. These factors will be collected to explore how new NP episodes interfere with individuals’ lives.

### Data analysis plan

#### O.1 Identification of candidate predictors

To identify candidate predictors that are clinically relevant, we will conduct two different comparisons. First, we will assess at baseline physical, psychological and social features during a period of remission and compare them with normative values from a control group using an independent t-test if the data satisfy parametric assumptions, or a non-parametric test, such as the Mann-Whitney U test, if they do not. Additionally, collected features within the physical and psychological domains will be assessed during a pain episode to evaluate the impact of pain on them. Comparisons with baseline (without pain) will be conducted using a paired t-test or a non-parametric alternative such as the Wilcoxon signed-rank test for within-subject comparisons. Differences will also be quantified by mean differences and 95% CIs. Physical, psychological and social features that differ between groups or within the same subject (during remission and pain episode) will then be considered as candidate predictors. Importantly, only baseline values of the candidate predictors collected will be used for prediction model development.

#### O.2 Development and internal validation of prediction models

We will use linear and ordinal regression models (with either a Least Absolute Shrinkage and Selection Operator (LASSO) penalty or a uniform shrinkage factor to account for any overfitting) to develop models for the prediction of continuous and ordinal outcomes, respectively. LASSO allows variable selection while incorporating shrinkage to deal with overfitting^73^, whereas the uniform shrinkage factor is estimated post-model fitting using bootstrapping and then applied to all predictor effects. The stability of performance of each development approach will be examined and compared. To ensure more stable models, the number of candidate predictors will be determined by the total sample size (number of participants and events) based on Riley *et al*^74^ (see sample size section). Candidate predictors will include those identified in O.1, and continuous predictors will be handled on their continuous scale allowing for potential non-linearity with fractional polynomials. Repeated cross-validation will be used to estimate tuning parameters (penalty terms) in the LASSO. Bootstrapping will be used for internal validation (repeating all model development steps, including any from O.1 to identify candidate predictors) to obtain a uniform shrinkage factor and to examine the stability of the model’s predictions and the potential for miscalibration in new data,^75^ and to produce optimism-adjusted measures of performance including R^2^, C-statistic (for ordinal outcome model), calibration-in-the-large and calibration slope, and prediction and classification instability plots and indices.^75^ Calibration plots with calibration curves will also be presented. The models’ predictive performance will be examined across different ethnic groups and by region, where possible, as part of fairness checks. For the ordinal outcome model, clinical utility will be examined using net benefit and decision curves, with a range of risk thresholds identified through consultations with patients and clinicians.^76^ Missing data in the candidate predictors is anticipated to be minimal, but if necessary, it will be managed using multiple imputation by chained equations method, which assumes the data are Missing at Random (MAR). Results will be averaged across imputation datasets to produce the final model and performance statistics. Multiple imputation at development is congenial with having no missing predictor data at deployment, which is as anticipated. For the ordinal outcome model, if the number of outcome events is sparse in some categories, we will collapse with neighbouring categories to address this issue. Specifically, we anticipate it may be necessary to collapse the no NP and mild NP categories, and the moderate NP and severe NP categories.

### Sample size

#### Sample size estimation for identification of candidate predictors (O.1)

Potential candidate predictors will be identified after testing physical and psychosocial factors for between-subject and within-subject differences. To consider a feature as a potential predictor, we expect a moderate effect size both for the comparison between subjects and within subjects. For the between-subjects analyses, we will consider 48 participants for the control group and 96 for the recurrent NP group. The sample size has been determined through a power analysis (G*Power), which assumes a moderate effect size of 0.5, an alpha level of 0.05 and a beta level of 0.8, with an allocation ratio of 2:1. For the within-subject comparison, we will conduct the second lab assessment on 34 participants with recurrent NP during an acute episode (α=0.05 and β=0.8).

#### Sample size estimation for the development and internal validation of prediction models (O.2)

To develop a prediction model for the continuous outcome of days with NP over the following 12 month (continuous outcome), we aim to recruit 250 participants with recurrent NP. The desired sample size is selected to target a shrinkage factor of ≥0.9 and small optimism in R² (≤ 0.05) to minimise overfitting.^74^ The calculation assumes an R² value of 0.40 based on previous data reported in a systematic review of prognostic models for neck pain,^77^ a mean of 35 days with NP and a residual SD of 15. The calculation suggests that about 16 candidate predictors can be considered with 250 participants. The sample size is also large enough to estimate the overall mean, which preliminary data suggests is about 35 days with NP over a 12-month period. Accounting for a drop-out rate at 20% due to the long follow-up, we aim to recruit 300 participants with recurrent NP over two testing sites (Birmingham and Essex). Uncertainty of predictions will be quantified using sampling distributions derived from bootstrapping.

For the severity of NP recurrences (ordinal outcome), we assume a predicted outcome distribution of 10% (no NP), 40% (mild NP), 40% (moderate NP) and 10% (severe NP), which was informed by preliminary data. Using a sample size of 250 participants (as above) allows 10 predictor parameters to minimise model overfitting assuming a Nagelkerke R-squared of 0.4 and targeting a 95% CI width of 0.12 for the overall risk,^74^ for a logistic regression model after collapsing the outcome to two categories as outlined above. We expect the ordinal regression model to allow more than 10 parameters, and we will consider 16 to be consistent with the continuous outcome and examine the impact of this using prediction and classification instability plots.^75^

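### The limit of 16 is stated in predictors, but the calculation supports 16 parameters, and fractional polynomials can use more than one parameter per predictor

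*Protocol article*

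**What the plan says.** The protocol's sample size section for O.2 sets the size of the continuous-outcome model: "we aim to recruit 250 participants with recurrent NP". The size is chosen to "target a shrinkage factor of ≥0.9 and small optimism in R² (≤ 0.05) to minimise overfitting". The planning values are given as "The calculation assumes an R² value of 0.40", with "a mean of 35 days with NP and a residual SD of 15". The result is "The calculation suggests that about 16 candidate predictors can be considered with 250 participants".

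The O.2 section of the data analysis plan makes this the operating rule: "the number of candidate predictors will be determined by the total sample size". It also says that "continuous predictors will be handled on their continuous scale allowing for potential non-linearity with fractional polynomials".

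The paragraph on the ordinal outcome, still in the sample size section, uses a different unit. It gives 10 predictor parameters for 250 participants, expects the ordinal model to support more parameters than that, and adopts 16 to match the continuous outcome. The article nowhere says whether polynomial terms or dummy variables count towards the 16.

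**The concern.** Criteria for expected shrinkage and optimism in R² depend on the number of candidate parameters, meaning every regression degree of freedom that is considered. The number of named variables does not enter them. The two counts agree only if each candidate is a single linear term or a two-level factor. Most features in Table 1 are continuous, so the option of fractional polynomials applies to most possible candidates.

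An analyst who follows the rule as worded could enter 16 predictors, open some of them to non-linear forms, and believe that the design targets still hold. The shrinkage and optimism targets are the stated reason for the sample size, so the unit of the limit matters.

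**Working it through.** **Inputs** (protocol, sample size section for O.2): n = 250; R² = 0.40; shrinkage S ≥ 0.9; optimism in R² ≤ 0.05; stated limit of about 16.

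**Formulas.** The article prints none. I used the standard closed-form criteria for a continuous outcome, with p the number of candidate parameters:

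- Apparent R²: R²app = [(n − p − 1) × R² + p] / (n − 1)
- Shrinkage: S = 1 + (p − 2) / [n × ln(1 − R²app)]
- Optimism: p × (1 − R²) / (n − 1)
- Residual SD estimated within 10%: n ≥ 234 + p

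**Reproducing the plan's 16.** With p = 16:

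- R²app = (233 × 0.40 + 16) / 249 = 109.2 / 249 = 0.4386
- S = 1 − 14 / (250 × 0.5772) = 0.903
- Optimism = 16 × 0.60 / 249 = 0.039
- Minimum n by criterion: shrinkage 242, optimism 193, residual SD 234 + 16 = 250. The largest is 250, as in the plan.

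The plan's figure is therefore correct when read as parameters.

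**Cross-check on the ordinal paragraph**, where the unit is explicitly parameters. Collapsing to two categories gives a 50:50 split (10% + 40% against 40% + 10%). The maximum R² is then 0.75, and a Nagelkerke R² of 0.4 corresponds to 0.4 × 0.75 = 0.30. For p = 10, n = 10 / [−0.1 × ln(1 − 0.30/0.9)] = 247. For p = 11 it is 272, which is above 250. The stated 10 parameters also reproduce, so both limits come from parameter-based criteria.

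**Reserve at n = 250.**

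| Parameters p | Shrinkage | Optimism | n needed |
|---|---|---|---|
| 16 | 0.903 | 0.039 | 250 |
| 17 | 0.897 | 0.041 | 260 |
| 20 | 0.879 | 0.048 | 312 |
| 21 | 0.873 | 0.051 | 330 |
| 24 | 0.856 | 0.058 | 383 |
| 32 | 0.815 | 0.077 | 523 |
| 64 | 0.693 | 0.154 | 1085 |

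Shrinkage misses its target from the 17th parameter. Optimism has some slack and misses only from the 21st.

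**How many parameters 16 predictors could use.** This is an assumption, because the article fixes neither the degree of the polynomials nor how they are counted. If only fitted coefficients count, a first-degree polynomial uses 1 and a second-degree one uses 2. If the search over powers also counts, they use 2 and 4. Sixteen continuous predictors therefore use between 16 × 1 = 16 and 16 × 4 = 64. The row for 24 is a mild case in which eight of the 16 use one extra parameter. It misses both targets.

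**The case against.** The strongest reply is that the authors may already mean parameters. The ordinal paragraph uses 16 in a sentence about parameters, and the fractional polynomial clause only permits non-linearity. If every candidate ended up using one parameter, both targets would be met. This stands, and it limits the point to an inconsistency of units with a conditional consequence. It does not remove the point, because the limit is worded in predictors both where it is derived and where it is applied.

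A second reply is that the plan uses LASSO or a uniform shrinkage factor, repeats all development steps in each bootstrap, and reports optimism-adjusted performance with instability plots. These steps would reduce the overfitting and make it visible. They would not deliver the planning targets, since the sample size was chosen so that little shrinkage should be needed.

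A reader might infer four stronger things that the protocol does not support:

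- **That the budget is exceeded two- to four-fold.** That is the upper part of the 16 to 64 range. It needs all 16 candidates to be continuous and non-linear, and the 64 also needs the search over powers to be counted.
- **That both targets fail together.** From 17 to 20 parameters only shrinkage fails.
- **That ethnicity, occupation and education level are sure to add dummy variables.** O.1 selects features with t-tests or rank tests, ethnicity is listed under demographics, and no coding is given. They may never enter.
- **That choosing candidates through O.1 contradicts a limit set by sample size.** O.1 can supply a pool from which the limit restricts how many are used. How a surplus is ranked is detail that an article may leave to the analysis plan.

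**Conclusion.** The point holds as an inconsistency of units, with moderate severity. The stated 16 is correct as a number of parameters for 250 participants at R² 0.40, and it is worded as a number of predictors in a plan that allows more than one parameter per predictor.

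The size of the consequence depends on an assumption about parameters per predictor. With one each, nothing is lost. With two to four each, expected shrinkage is 0.815 to 0.693 and optimism 0.077 to 0.154, and 523 to 1085 participants would be needed. The firm part needs no such assumption: a single parameter beyond 16 takes expected shrinkage below 0.9. All figures rest on the protocol's own R² of 0.40 and on 250 participants being analysed.

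**What to change.** In the O.2 analysis section and the O.2 sample size section, state the limit as 16 candidate predictor parameters for 250 participants. Say that every degree of freedom of a fractional polynomial and every dummy variable of a multi-level factor counts towards it, and reduce the number of predictors or non-linear terms to stay within it. If the team prefers to keep 16 predictors with non-linear terms, it should instead restate the expected shrinkage and optimism for the number of parameters actually considered.

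This is a change of wording and is best made before modelling begins. The cost is that fewer predictors, or fewer non-linear shapes, can be explored. How to divide the 16 among predictors and shapes can be left to the team.

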**Methods and analysis:**

The END-RNP study is a multicentre, prospective cohort study conducted from March 2025 to February 2028 at the University of Birmingham and the University of Essex (UK). 300 adults reporting two or more NP episodes in the previous year will be recruited from September 2025 to form the recurrent NP cohort, and 48 adults without a history of NP will provide normative data. Laboratory testing will be conducted for all participants when pain-free by assessing cervical kinematics and proprioception, neck-muscle strength, endurance and activation, pain processing, psychological and social factors. All recurrent NP participants will complete online questionnaires every 2 weeks for 12 months, recording days with NP, pain intensity/interference, healthcare use and other behavioural and environmental factors. Participants in the recurrent NP cohort who experience an acute NP episode during the 12-month follow-up will repeat the laboratory assessment. To develop the prediction models, candidate predictors will be the baseline measurements of any feature that shows either cross-sectional differences between recurrent NP and control groups or within-subject changes between the pain-free baseline and a pain episode. From the identified candidate predictors, two multivariable models will be developed using penalised regression, with (i) number of days with NP (linear regression) and (ii) NP severity (ordinal regression) as their respective dependent variables. Internal validation will use bootstrap resampling to estimate optimism-adjusted performance (R^2^, C-statistic and calibration slope), prediction instability and uncertainty, and clinical utility. The models from the END-RNP study will provide clinical prediction tools to help identify those at high risk of frequent and severe NP episodes and to inform the personalised prevention of recurrent NP.

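### 300 recruits with 20% drop-out leave 240 participants, not the 250 behind both prediction-model calculations; the stated targets are then narrowly missed

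*Protocol article*

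**What the plan says.** The protocol article, in the section on sample size for developing and validating the prediction models (O.2), first gives the number for the days-with-pain model: "we aim to recruit 250 participants with recurrent NP". It was chosen to "target a shrinkage factor of ≥0.9 and small optimism in R² (≤ 0.05) to minimise overfitting". The inputs are an R² of 0.40 ("The calculation assumes an R² value of 0.40") and "a mean of 35 days with NP and a residual SD of 15". The result is: "The calculation suggests that about 16 candidate predictors can be considered with 250 participants".

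The recruitment target follows: "Accounting for a drop-out rate at 20% due to the long follow-up, we aim to recruit 300 participants with recurrent NP". The abstract repeats it: "300 adults reporting two or more NP episodes in the previous year will be recruited from September 2025 to form the recurrent NP cohort". No other drop-out rate or recruitment target is given for this cohort.

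The severity model uses the same number: "Using a sample size of 250 participants (as above) allows 10 predictor parameters to minimise model overfitting". That calculation takes a Nagelkerke R² of 0.4, a 95% CI width of 0.12 for the overall risk, and a four-category outcome (10/40/40/10%) collapsed to two categories. The plan expects the ordinal model to allow more than 10 parameters and will consider 16.

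The section on O.2 model development says that total sample size will determine how many candidate predictors are used. It describes multiple imputation for missing candidate predictors only.

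**The concern.** The article calls both 250 and 300 numbers to recruit. The drop-out sentence makes sense only if 250 is the number to be analysed and 300 the number enrolled. On that reading the two do not fit a 20% loss: the allowance was added as 20% of 250 instead of being set so that 80% of recruits equals 250.

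This matters because the parameter allowances were set close to the limit of what 250 supports, and because sample size is meant to fix the number of candidate predictors. A shortfall of 10 could move the count from just inside the stated overfitting targets to just outside them.

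**Working it through.** **Inputs (protocol article, O.2 sample-size section).** Required n = 250; drop-out 20%; recruits 300; shrinkage target 0.9; R² = 0.40 with 16 predictors (days model); Nagelkerke R² = 0.4 with 10 parameters and a 50%/50% split after collapsing (10 + 40 against 40 + 10).

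**1. The recruitment figure**
- Reproducing the plan: 250 x 1.20 = 300.
- Inflation that keeps 250: 250/(1 - 0.20) = 312.5, so 313.
- Retained from 300: 300 x 0.80 = 240, which is 10 (4%) below 250.
- Loss at which 300 still gives 250: 1 - 250/300 = 16.7%.

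**2. Days model, shrinkage criterion.** The article does not print its formulas. I use the standard form for a linear model: S = 1 + (p - 2)/[n ln(1 - R²app)], with R²app = [R²(n - p - 1) + p]/(n - 1).
- n = 250, p = 16: R²app = (0.40 x 233 + 16)/249 = 0.4386; S = 0.9030. The plan's claim is reproduced.
- n = 240, p = 16: R²app = (0.40 x 223 + 16)/239 = 0.4402; S = 0.8994. The target is just missed.
- Smallest n with S of at least 0.9 at p = 16: 242.
- n = 240, p = 15: S = 0.9059, so the ceiling on this criterion is 15.

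**3. Days model, other criteria**
- Optimism in R²: p(1 - R²)/(n - 1) = 16 x 0.60/239 = 0.040 at 240, still within 0.05.
- Residual-SD precision: the criterion needs n = 234 + p. At p = 16 this is exactly 250, which suggests, but does not prove, that it set the number. At 240 it would allow 240 - 234 = 6 predictors. Yet with 16 predictors the multiplicative margin of error moves only from 1.0998 to 1.1023.
- Overall mean (35 days, residual SD 15, p = 16): the 95% CI is 33.13 to 36.87 at 250 and 33.09 to 36.91 at 240, a negligible change.

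**4. Severity model collapsed to two categories.** At 50% risk the maximum Cox-Snell R² is 0.75, so Cox-Snell R² = 0.4 x 0.75 = 0.30. Allowed parameters = 0.1 x n x [-ln(1 - 0.30/0.9)] = 0.1 x n x 0.4055.
- n = 250: 10.14, so 10. The plan's figure is reproduced.
- n = 240: 9.73, so 9. With 10 parameters, expected shrinkage is 0.898 (0.901 at 250).

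**5. CI width for overall risk:** 2 x 1.96 x sqrt(0.25/n).
- n = 250: 0.124. n = 240: 0.127.
- A width of 0.12 needs (1.96/0.06)² x 0.25 = 266.8, so 267. Most of the gap from 0.12 is already there at 250.

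**The case against.** The strongest case on the other side is that nothing of substance changes. Several parts of it stand.

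- Expected shrinkage at 240 is 0.8994 (days model) and 0.898 (collapsed model). Both round to 0.90, the article says about 16 predictors, and R² = 0.40 is itself an assumption. On shrinkage alone the days model is 2 participants short (242 against 240).
- The figure of 10 does not govern the severity model, because the plan knowingly considers 16 parameters and will examine instability. Moving 10 to 9 changes no planned analysis.
- If total sample size in the O.2 development section means the achieved sample, the predictor count will adjust to actual retention. LASSO or uniform shrinkage, bootstrap optimism correction and instability checks would also detect and temper slight extra overfitting.
- Outcomes come from questionnaires every 2 weeks, so some participants who drop out will leave partial data. The figure of 240 treats them as giving no usable outcome. The article does not say how partial outcome data would be used.

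Three stronger readings are tempting and not supported. A reader might infer that the study cannot deliver model development as planned; misses of this size do not show that. A reader might infer that 15 is the new ceiling for the days model; that holds on shrinkage alone, since under the residual-SD criterion 15 predictors need 249. The article does not settle whether that criterion was used: it states a residual SD, but that value also serves the precision of the mean. A reader might also blame drop-out for missing the CI width of 0.12; drop-out adds only about 0.003 to a width that is 0.124 at 250.

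None of this corrects the recruitment figure, which remains inconsistent with the stated drop-out rate.

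**Conclusion.** The point holds as an arithmetic inconsistency with small consequences. A required 250, a 20% loss and 300 recruits cannot all be true: 300 gives 240 at 20% loss, and gives 250 only at a loss of 16.7% or less. At 240 the shrinkage target of 0.9 is missed in the third decimal with 16 predictors, and the collapsed severity model supports one parameter fewer.

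The conclusion rests on reading 250 as the analysable number, on drop-outs giving no usable 12-month outcome, and on the standard form of the shrinkage criteria, which reproduces the plan's allowances at 250. Severity is minor to should-fix: the effect is slight, but the number is one that the plan uses to set its predictor count.

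**What to change.** Choose one of two changes in the O.2 sample-size section:

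1. State that recruiting 300 tolerates a drop-out of about 16.7%, and leave the figures for 250 as they are.
2. Keep 20% drop-out and restate the O.2 figures for 240 analysable participants, with the ceiling under each criterion used: 15 for the days model on shrinkage alone, and 9 for the collapsed severity model. If a residual-SD precision criterion was used (n = 234 + p), address it separately and say how it is treated at 240. Give the CI width for overall risk as 0.127, noting that it is 0.124 at 250.

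In either case, say in the O.2 development section that the analysable number, not the recruited number, sets the count of candidate predictors.

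The cost is a few sentences and, under the second option, a slightly smaller stated allowance. Neither option needs more participants. Keeping both 250 and 20% would mean a target of 313, which is 13 more recruits.
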